#### **4.1 Enrollment**

This prospective observational study will be conducted in the operating rooms of the first and second floors of the Company's hospital Hospital of Padua.

All patients requiring thyroidectomy will be enrolled.

No clinical decision will be made based on the data collected for this study. In fact, during the study only information that is normally detected during a routine anesthetic visit will be recorded.

## **5. Materials and methods**

During the routine anaesthesiology visit, upon collection of the consent, the following parameters will be recorded on the data sheet.

- Opening mouth (cm)
- Distance thyreomental (cm)
- Test of Mallampati (Annex 2)
- Mobility of the neck (<80 °; 80-90 °; > 90 °)
- Inability to prognath
- Body weight (kg)
- History of previous intubation difficult
- Tracheal deviation to the chest radiography
- Diameter of the goiter (cm)
- Presence of mediastinal goiter
- Benign or malignant nature of the thyroid pathology

On the day of the surgical intervention after tracheal gold intubation the presence or absence of difficulty in the maneuver will be reported on the data sheet ; in particular:

- Cormack Scale (Annex 1)
- Number of attempts necessary to successfully perform the intubation
- Time elapsed since the induction of general anesthesia and intubation successfully
- If advanced airway instrument were used and which ones

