## **2. Background**

### **2.1 Definitions**

For difficult intubation [1], we mean a procedure that has been characterized by a difficult laryngoscopy or has required at least four attempts or more than five minutes for its execution regardless of the degree of experience of the anesthesiologist.

Difficult laryngoscopy refers to the impossibility of highlighting the glottis with the conventional curved blade laryngoscope. It corresponds to grades 3 and 4 of the classification of Cormack and Lehane (Annex 1) in which it is possible to highlight respectively only the epiglottis or the language alone.

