### **3. Objectives of the study and hypothesis**

#### **3.1. Primary objective and hypothesis**

Evaluation incidence difficult intubation in the population with thyroid pathology compared to the data provided by the literature in the general population

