## 5.2 Statistics

### 5.2.1 Sample Size

The estimates of study power and sample size were based on an assumption of a difference of 4% in the incidence of difficult intubation between the general population of patients undergoing surgery

[1] and the population of patients undergoing thyroid surgery [4], We use an  $\alpha$ -value of 5%, a power

( $1-\beta$  error) of 95%, a drop out percentage of 5%. The results of the analysis indicated that a sample size of 515 patients was necessary to estimate the prevalence of DTI in a population of patients undergoing thyroid surgery.

The data for each continuous variable will be analyzed for a normal distribution using the Kolmogorov-Smirnov test. Results for continuous variables with normal distributions will be expressed as mean (standard deviation) values; those with non-normal distributions will be expressed as median (interquartile range) values. Analysis of data with a normal or a non-normal distribution will be performed using the two-tail Student's t-test and the Mann-Whitney U test, respectively. The results for analyses of categorical variables will be reported as numbers (percentages) and were compared between groups using Chi-square tests. To determine the strength and direction of association between two variables, we will use the Bravais-Pearson's correlation test for variables with a normal distribution and Spearman's rank correlation test for variables that will not meet the assumptions of a normal distribution.

To determine the relationships between the dependent categorical variable (i.e., DTI) and one or more independent categorical variables (i.e., DTI predictors), we will perform a multiple logistic regression analysis to calculate odds ratios (ORs) with 95% confidence intervals (CIs). All statistical analyses will be performed using R version 3.4.0 (2017-04-21). P-values < 0.05 will be considered to indicate a statistically significant result.

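### The five-minute criterion is defined on execution of the intubation, but the only time listed starts at induction: difficult intubations can be over-counted, or the third criterion has no data

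*Protocol*

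**What the plan says.** Protocol section 2.1 (Definitions) gives a three-part definition joined by 'or'. A difficult intubation is "a procedure that has been characterized by a difficult laryngoscopy or has required at least four attempts or more than five minutes". Difficult laryngoscopy means Cormack and Lehane grade 3 or 4. The time limit is attached to the procedure itself: it counts when the intubation "has required at least four attempts or more than five minutes for its execution".

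Section 5 (Materials and methods) says that on the day of surgery "the presence or absence of difficulty in the maneuver will be reported on the data sheet" and then itemises what is recorded: Cormack grade, number of attempts, one time, and any advanced airway instruments. The time is "Time elapsed since the induction of general anesthesia and intubation successfully". No other time or duration is listed.

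The outcome serves the primary objective in section 3.1, "Evaluation incidence difficult intubation in the population with thyroid pathology compared to the data provided by the literature in the general population". It is also the dependent variable of the logistic regression in section 5.2.1.

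**The concern.** The quantity in the definition and the quantity recorded are different. The recorded interval is the execution time plus whatever passes between induction and the first laryngoscopy. It can equal or exceed the execution time but never fall below it. Because the components are joined by 'or', a long interval alone is enough to classify a patient as difficult.

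The plan as written leaves two possibilities. If the five-minute limit is applied to the recorded interval, misclassification on this component goes one way only, towards over-counting. If it is not, the third component has nothing listed behind it. A later analysis plan cannot repair this, because execution time cannot be derived from the items listed.

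The primary comparison is with an external literature figure, so there is no concurrent control group in which the same error would occur and cancel.

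**Working it through.** **1. The two clocks side by side**

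- Definition (section 2.1): more than five minutes for execution of the intubation.
- Recorded item (section 5): induction of general anaesthesia to successful intubation.
- Recorded interval = time from induction to first laryngoscopy + execution time. The first term is zero or positive.
- Illustration: if the first term were 3 minutes (an assumption), any manoeuvre longer than 5 − 3 = 2 minutes would exceed the limit on the recorded clock.

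**2. The plan's own figure**

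Section 5.2.1 gives 515 patients from "an assumption of a difference of 4% in the incidence of difficult intubation", alpha 5%, power 95% and 5% dropout. The base rate, the test and its sidedness are not stated, so 515 can be neither confirmed nor refuted. For example, a one-sample, one-sided test of 6% versus 10%, divided by 0.95 for dropout, gives 515; a one-sample, two-sided test of 5% versus 9% gives 504 before dropout. The present point does not depend on this.

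**3. Effect on incidence**

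Let p be the true incidence under section 2.1, and q the share of truly non-difficult cases whose induction-to-intubation time exceeds five minutes.

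Observed incidence = p + (1 − p)q, so bias = (1 − p)q.

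Neither p nor q is fixed by the protocol. Section 2.2 gives 0.5% to 20% for the general population; the section on thyroid pathology gives 0% to 12.9%. With p = 5% assumed:

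| q (assumed) | Observed incidence | False positives in 515 |
|---|---|---|
| 2% | 0.05 + 0.95 × 0.02 = 6.9% | about 10 |
| 5% | 0.05 + 0.95 × 0.05 = 9.75% | about 24 |
| 10% | 0.05 + 0.95 × 0.10 = 14.5% | about 49 |

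How large q might be is open. If induction-to-tube time in non-difficult cases were roughly normal, the share above five minutes would be 0.4% for mean 3 and SD 0.75 min, 6.7% for mean 3.5 and SD 1, and 15.9% for mean 4 and SD 1. All three are assumptions.

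**4. Effect on the primary comparison**

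A bias of 4 percentage points needs q = 0.04/(1 − p): 4.0% at p = 0.5%, 4.2% at p = 5%, and 5.0% at p = 20%.

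- *Creating a difference.* Suppose true incidence equals the reference. Use a two-sided one-sample z test at 5% (assumed) and n = 515 × 0.95 ≈ 489. At reference 5% and q = 2%, the null SE is √(0.05 × 0.95/489) = 0.00986 and the SE at 6.9% is √(0.069 × 0.931/489) = 0.01146. The chance of a significant excess is 1 − Φ((1.96 × 0.00986 − 0.019)/0.01146) ≈ 49%. It is about 18% at q = 1% and 98% at q = 5%. At reference 12.9% the corresponding figures for q = 1%, 2% and 5% are about 10%, 22% and 79%.
- *Masking a difference.* If true incidence were 5% against a reference of 9%, q = 4.2% would give 0.05 + 0.95 × 0.042 ≈ 9.0%, and the difference would disappear.

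**5. Effect on predictor associations**

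If q is the same in patients with and without a predictor (non-differential), odds ratios move towards 1. For an illustrative 20% versus 8%, the true OR is (0.20/0.80)/(0.08/0.92) = 2.88. At q = 5% the risks read 24% and 12.6%, OR 2.19. At q = 10% they read 28% and 17.2%, OR 1.87. If q differs by predictor, the direction is not fixed.

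**The case against.** The strongest reply is that the protocol never says the recorded interval is tested against five minutes. Section 5 speaks of reporting difficulty in the manoeuvre, and one listed item, advanced instruments, is not part of the definition. The time could therefore be descriptive, with difficulty judged directly. The English is also rough, section 2.1 does not say when execution begins, and the data sheet itself is not shown. This stands to a degree: a reader might infer that easy intubations *will* be counted as difficult, and the text supports only that they *can* be. It does not remove the mismatch. The time is listed beside Cormack grade and attempts, the other two components, and no other listed time could serve the third.

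Three further inferences are tempting and not supported:

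- *That the bias produces the whole planned 4-point difference.* The size of q is undocumented, and the scenarios above run from 0.4% to about 16%. The direction of the planned difference is not stated either. Section 5.2.1 takes the thyroid figure from reference [4], for which the protocol elsewhere reports 0%, so over-counting might hide a difference instead.
- *That every predictor association is diluted.* This needs non-differential error. The extra interval may include mask ventilation, which could vary with recorded predictors such as body weight.
- *That the extra stamp is entirely free.* Someone has to note the time. Section 4.1 limits recording to what a routine anaesthetic visit detects, although section 5 already lists items from the day of surgery.

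**Conclusion.** The point holds as a mismatch between a component of the primary outcome and the variable collected for it. That part rests on the text alone. The consequence is conditional: either incidence is biased upward by (1 − p)q, or the time component has no listed data. The size is unknown because no document gives induction-to-laryngoscopy times. Under the assumed p = 5%, even q = 2% moves incidence from 5% to 6.9%, which is material for a study planned on a 4-point difference. The bias may create or mask a difference from the literature reference. It can distort predictor associations, towards the null only if the misclassification is non-differential.

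**What to change.** Reconcile sections 2.1 and 5:

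- Record two clock times: start of the first laryngoscopy and successful intubation.
- State that the five-minute criterion applies to their difference.
- Keep induction-to-intubation time as a descriptive item that does not enter the outcome.

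If some patients have already been recorded on the induction clock only:

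- An interval of five minutes or less rules the time criterion out, because execution cannot have been longer.
- Where the interval is longer and neither Cormack grade nor attempts qualifies, treat the time component as indeterminate.
- Report incidence for the whole cohort on one common definition (Cormack grade or attempts), so that two definitions are not mixed. Add bounds that count none, then all, of the indeterminate cases as difficult.

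The cost is one extra time stamp on the data sheet, and someone to note it. It changes measurement only, not patient care.

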### **5.1 Data collection**

Data will be collected in a data collection form. Patients will be assigned with a numerical code to facilitate subsequent processing; the data will be stored in an anonymised form.

## 5.2 Statistics

### 5.2.1 Sample Size

The estimates of study power and sample size were based on an assumption of a difference of 4% in the incidence of difficult intubation between the general population of patients undergoing surgery

[1] and the population of patients undergoing thyroid surgery [4], We use an  $\alpha$ -value of 5%, a power

( $1-\beta$  error) of 95%, a drop out percentage of 5%. The results of the analysis indicated that a sample size of 515 patients was necessary to estimate the prevalence of DTI in a population of patients undergoing thyroid surgery.

The data for each continuous variable will be analyzed for a normal distribution using the Kolmogorov-Smirnov test. Results for continuous variables with normal distributions will be expressed as mean (standard deviation) values; those with non-normal distributions will be expressed as median (interquartile range) values. Analysis of data with a normal or a non-normal distribution will be performed using the two-tail Student's t-test and the Mann-Whitney U test, respectively. The results for analyses of categorical variables will be reported as numbers (percentages) and were compared between groups using Chi-square tests. To determine the strength and direction of association between two variables, we will use the Bravais-Pearson's correlation test for variables with a normal distribution and Spearman's rank correlation test for variables that will not meet the assumptions of a normal distribution.

To determine the relationships between the dependent categorical variable (i.e., DTI) and one or more independent categorical variables (i.e., DTI predictors), we will perform a multiple logistic regression analysis to calculate odds ratios (ORs) with 95% confidence intervals (CIs). All statistical analyses will be performed using R version 3.4.0 (2017-04-21). P-values < 0.05 will be considered to indicate a statistically significant result.

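### The plan fixes the equal-variance Student's t-test for continuous predictors in very unequal groups, and its normality check does not look at spread; Welch's test in that branch is a cheap improvement

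*Protocol*

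**What the plan says.** The analysis text stands in Protocol section 5.2.1. It opens with a normality screen: "The data for each continuous variable will be analyzed for a normal distribution using the Kolmogorov-Smirnov test". Variables judged normal and non-normal are then analysed by a comparison that "will be performed using the two-tail Student's t-test and the Mann-Whitney U test, respectively". The decision rule is "P-values < 0.05 will be considered to indicate a statistically significant result". The section names no unequal-variance test and no check of spread.

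The two groups are not named. The only grouping that the objectives imply is difficult against not difficult intubation. The continuous candidates in section 5 are mouth opening, thyromental distance, body weight and goiter diameter, and section 3.2 adds the NC/TMD ratio. These comparisons serve the secondary objective, the search for predictors. A multiple logistic regression is also planned, but it is described for categorical predictors.

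**The concern.** Student's t-test estimates one common variance from both groups. When one group is many times larger, that estimate comes almost wholly from the larger group, while the uncertainty of the mean difference comes almost wholly from the smaller one. If the two spreads differ, the standard error is wrong and so is the p-value.

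The error can go either way. If difficult cases are more variable, a measurement with no difference in mean is declared a predictor too often. If they are less variable, a real predictor is missed too often. The Kolmogorov-Smirnov screen tests shape, so it gives no warning of either. The stake is the list of continuous predictors reported under the secondary objective.

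**Working it through.** **Inputs from the Protocol.** Section 5.2.1: "a sample size of 515 patients was necessary to estimate the prevalence of DTI in a population of patients undergoing thyroid surgery", derived from "an assumption of a difference of 4% in the incidence of difficult intubation between the general population of patients undergoing surgery", with 5% alpha, 95% power and 5% dropout. Section 2.2 gives difficult intubation of 0.5% to 20% in the general population, and section 2.3 gives 0% to 12.9% in thyroid studies.

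**The plan's own figure.** The base rate behind the 4-point difference and the sidedness of the test are not stated, so 515 cannot be rebuilt from the stated inputs alone. It can be reached. The one-sample formula is n = [z_α√(p0q0) + z_β√(p1q1)]² / (p1 − p0)². One-sided, 6% against 10%, it gives 489, and 489/0.95 = 515 after rounding up. Two-sided, 4.8% against 8.8%, it gives 490, and 490/0.95 = 516 after rounding up. I take 515 as given; evaluable patients are 515 × 0.95 ≈ 489.

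**Assumptions not in the Protocol.**
- Difficult intubation of 5% or 9%: 489 × 0.05 ≈ 24 against 465, and 489 × 0.09 ≈ 44 against 445.
- An SD ratio r (difficult/easy) of 0.67 to 1.5, because no SDs are given.
- Normal data, unless stated otherwise.

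**Closed form for Student's test.** With the easy group's SD set to 1:
- pooled variance: s² = [(n1 − 1)r² + (n2 − 1)] / (n1 + n2 − 2)
- variance the test uses: P = s²(1/n1 + 1/n2)
- true variance: T = r²/n1 + 1/n2
- type I error ≈ 2[1 − Φ(1.96√(P/T))]

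For 24 against 465 and r = 1.5:
- s² = (23 × 2.25 + 464)/487 = 1.059
- P = 1.059 × 0.04382 = 0.0464
- T = 0.09375 + 0.00215 = 0.0959
- √(P/T) = 0.696, and 1.96 × 0.696 = 1.363, so the error is 17.3%

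**Simulated type I error, equal means, nominal 5%:**

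| Groups | r | Student (closed form) | Student | Mann-Whitney | Welch |
|---|---|---|---|---|---|
| 24 v 465 | 0.67 | 0.5% | 0.6% | 1.5% | 5.1% |
| 24 v 465 | 1.0 | 5.0% | 5.0% | 5.0% | 5.1% |
| 24 v 465 | 1.25 | 10.9% | 11.3% | 8.0% | 5.1% |
| 24 v 465 | 1.5 | 17.3% | 17.6% | 10.3% | 5.2% |
| 44 v 445 | 0.67 | 0.7% | 0.7% | 1.8% | 5.2% |
| 44 v 445 | 1.0 | 5.0% | 5.2% | 5.1% | 5.2% |
| 44 v 445 | 1.25 | 10.2% | 10.3% | 7.4% | 4.8% |
| 44 v 445 | 1.5 | 15.8% | 15.3% | 9.6% | 5.0% |

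**Other event counts.** The Protocol's ranges allow from almost none to 98 events (489 × 0.20). At r = 1.5, Student's error is 18.1% with 10 events, 14.8% with 63 (12.9%) and 12.0% with 98.

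**Power when difficult cases are less variable.** Take r = 0.67, 24 events and a shift of 0.4 SD. T = 0.4489/24 + 1/465 = 0.02085, so the true standard error is 0.144. Student's uses √P = √0.04268 = 0.207, and its rejection limit is 1.96 × 0.207 ≈ 0.405, just above the shift itself. Simulated power is 48% for Student's and 76% for Welch.

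**What the screen does.** On unrounded normal data it rejected in at most 0.6% of runs, so the two-stage rule behaves as Student's. On truly normal data with an assumed mean of 4.5 cm and SD of 0.7 cm, it rejected 6% to 7% of the time when values were read to 0.1 cm and 100% when read to 0.5 cm. Section 5 gives the unit but no reading precision, so measuring habit can decide which test is run.

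**Skewed data.** With identical lognormal groups (24 v 465, log-SD 0.4 to 1.0), Welch on raw values gives 5.9% to 11.2% type I error and Mann-Whitney 4.6% to 5.0%. For a 0.6 log-SD shift (log-SD 0.4 to 0.8), power is 50% to 69% for Welch and about 79% for Mann-Whitney. Brunner-Munzel held about 4% to 6% type I error in every setting simulated.

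**The case against.** The strongest reply is that the defect is conditional. Every harmful figure needs unequal spread, and the Protocol gives neither SDs nor a reason to expect it. With equal spreads both planned tests hold 5%. That stands, and it limits the weight of the point. It does not remove it: the Protocol does not rule unequal spread out either, and a ratio of 1.25 already doubles Student's error.

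A second reply is that Mann-Whitney is sound. Under identical distributions it holds 5%. Its 9% to 11% at a ratio of 1.5 is an error only against a null of equal centre, and a variable whose spread differs by difficulty is not wholly unrelated to difficulty. This stands, so the point rests on the t-test branch.

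A third is that Welch for every variable could do harm. For skewed measurements it could, as the lognormal results show, so a blanket switch is not supported.

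A fourth is that R, the named software, defaults to Welch and that an analysis plan not shown may settle the form. But the Protocol says Student's, which in standard usage means equal variances. If Welch was meant, the wording needs the same correction. The regression does not fill the gap, because it is described for categorical predictors.

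A reader might also infer that the full screening rule always carries Student's error of about 17%. It does not. At 24 v 465 and a ratio of 1.5, values read to 0.1 cm give about 16%, and values read to 0.5 cm go to Mann-Whitney and give 9.9%.

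**Conclusion.** The point holds as a cheap improvement. The Protocol fixes an equal-variance test where group sizes will be very unequal and provides nothing that would detect unequal spread. Under the assumptions above, Student's type I error runs from under 1% to 18% over SD ratios of 0.67 to 1.5, while Welch stays near 5%. The same pattern appears at 10, 63 and 98 events, so it does not hang on the assumed 5% to 9% rate.

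A reader might conclude that the planned tests will give false predictors in this study. The documents do not support that: the SD ratio and the event count are both assumptions, and with equal spreads nothing is wrong. The consequence is confined to univariate comparisons under the secondary objective. The primary objective, the incidence of difficult intubation, is unaffected.

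**What to change.** In section 5.2.1:
- Replace Student's t-test with Welch's unequal-variance t-test for predictors compared by means, and report the mean difference with its 95% CI.
- Name in advance which predictors will be compared by ranks because skewness is expected (goiter diameter or weight, for example). Do not let a normality p-value choose the test.
- Keep a rank test for those predictors, preferably Brunner-Munzel, and do not apply Welch to their raw values.
- State that the groups compared are difficult and not difficult intubation.

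The cost is a few sentences of text and about 3 points of power if spreads are equal (83% to 80% for a 0.6 SD shift with 24 events). No extra data or patients are needed.

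### The multivariable logistic model is worded for categorical predictors, although mouth opening, thyromental distance, weight and goiter diameter are recorded as measurements

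*Protocol*

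**What the plan says.** The analysis text stands under Protocol section 5.2.1. For the model it states: "we will perform a multiple logistic regression analysis to calculate odds ratios (ORs) with 95% confidence intervals (CIs". It describes the variables in that model as a "dependent categorical variable (i.e., DTI) and one or more independent categorical variables (i.e., DTI predictors", which equates the predictors with categorical variables. No continuous covariate is named for the model, and no power is stated for it.

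Section 5 (Materials and methods) lists four candidate predictors on a measured scale: "Opening mouth (cm", "Distance thyreomental (cm", "Body weight (kg" and "Diameter of the goiter (cm". Only neck mobility is banded in advance; the other items are classes or yes/no findings.

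Elsewhere in section 5.2.1 measured variables stay measured: "Analysis of data with a normal or a non-normal distribution will be performed using the two-tail Student's t-test and the Mann-Whitney U test, respectively". The correlation analyses (Pearson or Spearman) do the same.

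The model serves section 3.2, the secondary objective of identifying predictors of difficult intubation. That section also names NC/TMD as a predictor to be examined.

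**The concern.** The regression sentence does not fit the data it is to be applied to. An analyst who follows it has two options for each of the four measurements: cut it into categories, or leave it out of the model. A measurement such as thyromental distance would then be compared between groups on its full scale and enter the adjusted model, if at all, only in coarsened form.

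Coarsening discards information, and the number of difficult intubations is likely to be modest. It also makes the odds ratio depend on where the cut is placed, and it adjusts less fully for the variable that was cut. What is at stake is the ability of the one multivariable analysis to show which measurements predict difficult intubation.

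**Working it through.** **1. The plan's own figure.** The stated 515 patients rest on "an assumption of a difference of 4% in the incidence of difficult intubation", with 5% alpha, 95% power and 5% dropout. This concerns the primary objective. The two underlying rates are not stated, so 515 cannot be confirmed. As an illustration, the one-sample formula [z_a√(p0·q0) + z_b√(p1·q1)]² / d² with assumed rates of 6% and 10%, one-sided, gives 489, and 489 / 0.95 = 515. The present point does not depend on this. It needs only the number of patients: 515 enrolled, or 515 × 0.95 ≈ 489 after dropout.

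**2. Number of events (incidence assumed).** Section 2.3, on thyroid pathology, reports 0% to 12.9% in earlier studies. At 5%, 489 × 0.05 ≈ 24 and 515 × 0.05 ≈ 26 events. At 8%, 515 × 0.08 ≈ 41. At 12.9%, 515 × 0.129 ≈ 66.

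**3. Information kept by a cut.** For a normal predictor with a linear logit, the asymptotic relative efficiency of a cut at c, with a fraction q above it, is φ(c)² / [q(1 − q)].

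- Median: 0.3989² / 0.25 = 0.637; 0.637 × 515 ≈ 328 effective patients
- Quartile: 0.3178² / 0.1875 = 0.539; 0.539 × 515 ≈ 278
- 10% tail: 0.1755² / 0.09 = 0.342; 0.342 × 515 ≈ 176

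**4. Power (%) by simulation.** One normal predictor, univariable, two-sided 5%. The rows at 489 use a logistic Wald test with 2,000 replicates; the rows at 515 use the equivalent score test with 4,000.

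| Patients | Incidence | OR per SD | Continuous | Median split | Loss (points) |
|---|---|---|---|---|---|
| 489 | 5% | 1.7 | 69 | 46 | 23 |
| 489 | 7% | 1.5 | 61 | 42 | 19 |
| 489 | 7% | 1.7 | 83 | 63 | 20 |
| 515 | 5% | 1.5 | 52 | 35 | 17 |
| 515 | 8% | 1.5 | 68.8 | 48.9 | 19.9 |
| 515 | 8% | 1.7 | 89.0 | 70.7 | 18.3 |
| 515 | 12.9% | 1.5 | 85.6 | 68.1 | 17.5 |
| 515 | 12.9% | 1.7 | 97.4 | 86.8 | 10.6 |
| 515 | 12.9% | 2.0 | 99.9 | 98.1 | 1.8 |

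The Monte Carlo standard error of each power is about 1 point (√(0.5 × 0.5 / 2000) = 1.1 points at most). A 10% tail cut loses more: at 515 patients, 8% and OR 1.5, power is 41.8%, a loss of 68.8 − 41.8 = 27 points.

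**The case against.** The strongest reply is that the sentence is a loose, generic description of logistic regression. The protocol never says that measurements will be cut or grouped, and the same section keeps them continuous elsewhere. That is a fair reading of intent, and it limits the claim: categorisation is what the wording implies, not a declared decision. It does not remove the mismatch, because the wording leaves no place for a measured predictor.

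It can also be said that the power figures come from a univariable test, whereas univariately the plan already uses the full scale. This stands. The loss is confined to the multivariable model, which was not simulated, so the figures show the cost of a cut and are not power estimates for the planned regression. If risk truly steps at a threshold, a cut placed there would lose less.

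Two stronger readings are tempting, and the protocol supports neither.

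- **Cut-points taken from the data, with inflated false positives.** The protocol does not say so. External limits are at least as plausible: section 2.3 quotes a distance threshold from the literature, and neck mobility is banded in advance. Cut-points may also be left to a statistical analysis plan, so their absence is not in itself the fault.
- **A repeat of a conflict caused by differing thresholds.** Section 2.3, on thyroid pathology, attributes the conflicting results to small numbers, with studies of 50 to 326 patients, and does not mention thresholds.

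**Conclusion.** The point holds as a badly fixed method, not as missing detail. The sentence in section 5.2.1 conflicts with the measured predictors in section 5 and with the handling of continuous variables in the same section. Read as written, it forces four measurements to be categorised or dropped from the only multivariable model for the secondary objective.

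A median split keeps about 64% of a predictor's information. It costs about 17 to 23 points of power at 489 to 515 patients, 5% to 8% incidence and OR 1.5 to 1.7 per SD. This rests on an assumed incidence, a normal predictor, a linear logit and a univariable test. Where power is already near 100%, the loss nearly vanishes (1.8 points at 12.9% and OR 2.0).

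A reader might infer that the stated 95% power is undermined. It is not: that figure belongs to the primary incidence objective, which is unaffected. Nor is anything lost for good, because the raw measurements are recorded. The change is worth making, but the matter is confined to the secondary objective.

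**What to change.** Reword the regression sentence to *categorical and continuous predictors*. Enter mouth opening, thyromental distance, body weight and goiter diameter as continuous linear terms, and report each odds ratio per stated unit (for example per cm or per kg). Section 5 lists 11 candidate predictors against perhaps 24 to 66 events, so limit any check for non-linearity to what the observed event count supports. If a bedside cut-off is wanted, derive it afterwards and label it exploratory.

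For these four variables the cost is one sentence, with the same data and software.

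NC/TMD is a separate matter. If it is modelled, keep it continuous and do not enter it alongside thyromental distance in the same model, because that distance is its denominator. Read as neck circumference over thyromental distance, the ratio also needs neck circumference, which section 5 does not list. Modelling it would therefore require one more item on the data sheet.
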